**Date of Signature 2022-09-05**

**Institution/Affiliation Peking University People’s Hospital**

**City, Province, Country Beijing, China**

# Study Synopsis

| **Study title** | Luspatercept for promoting hematopoietic recovery in patients with poor hematopoietic reconstitution after allogeneic hematopoietic stem cell transplantation——a prospective single-arm clinical study |
| --- | --- |
| **Indication** | Poor hematopoietic reconstitution after allogeneic hematopoietic stem cell transplantation |
| **Study applicant** | Peking University People’s Hospital |
| **Study center** | Peking University People’s Hospital |
| **Number of subjects planned** | Approximately 64 subjects |
| **Study duration** | Estimated to be 3 year |
| **Objectives** | **Primary objective:**  To evaluate the efficacy and safety of luspatercept for promoting hematopoiesis recovery in patients with poor hematopoietic reconstitution after allogeneic hematopoietic stem cell transplantation (allo-HSCT).  **Exploratory objectives:**  To evaluate the influence of luspatercept in the bone marrow microenvironment among patients with poor hematopoietic reconstitution after allo-HSCT. |
| **Study design** | This is a prospective single-arm clinical study to evaluate luspatercept for promoting hematopoietic recovery in patients with poor hematopoietic reconstitution after allo-HSCT.  Approximately 64 subjects will receive luspatercept treatment.  The dose of luspatercept ranged from 0.7 to 1.4 mg/kg subcutaneously on the basis of routine supportive therapy.  The complete blood count will be monitored every 7 days within 20 days from the beginning of luspatercept treatment.  Adverse events were evaluated following the National Cancer Institute Common Toxicity Criteria version 5.0. |
| **Inclusion criteria** | Subjects eligible for enrolment in this study must meet all of the following criteria:   1. Poor hematopoietic reconstitution after HSCT receiving luspatercept treatment 2. Aged 18-60 years 3. Comply with the study and follow-up procedures |
| **Exclusion criteria** | Subjects meeting any of the following criteria are ineligible for this study:   1. Severe organ injury 2. Uncontrolled active infections 3. Hypersensitivity to luspatercept |
| **Study treatment** | **Luspatercept treatment**  Poor hematopoietic reconstitution after HSCT will be enrolled, and luspatercept will be administered subcutaneously. The complete blood count (CBC) will be monitored every 7 days.  The primary endpoint was defined as hematologic improvement-erythroid (HI-E), which included the achievement of red blood cell transfusion independence (RBC-TI) for patients requiring RBC transfusions before administration, as well as a mean Hb increase ≥ 1.5 g/dL for RBC-TI patients at the first administration. The secondary endpoints included proportions of patients who achieved absolute increases in neutrophil ≥ 0.5 × 10^9^/L and platelet counts ≥ 30 × 10^9^/L, respectively; proportions of patients who achieved HI-neutrophil (HI-N) and HI-platelet (HI-P) counts; measurements of white blood cell (WBC), absolute neutrophil and platelet counts; and mean changes from baseline. |
| **Sample size determination** | The number of patients eligible for luspatercept treatment was estimated based on the 20-day hematologic improvement-erythroid (HI-E) reported by Vanstraelen et al.[^1^](#_ENREF_1_1) The present study was planned to detect a 20-day ORR of 28% in patients receiving luspatercept treatment from the reference rate of 14%, controlling for type I and II error rates at 5 and 20%, respectively. Considering an expulsion rate of 10%, a total of 64 patients were planned to be enrolled. |
| **Statistical analysis** | Statistical analyses will be performed based on the intent-to-treat (ITT) population.  **Primary Efficacy Analysis:**  Primary Outcome Measure:  1. Hematologic improvement-erythroid (HI-E)   1. For patients requiring RBC transfusions before administration: the achievement of red blood cell transfusion independence (RBC-TI) 2. For RBC-TI patients at the first administration: mean Hb increase ≥ 1.5 g/dL   **Secondary Efficacy Analysis:**  1. Hematologic improvement-leukocyte  1) Proportions of patients who achieved absolute increases in neutrophil ≥ 0.5 × 10^9^/L;  2) Proportions of patients who achieved HI-neutrophil (HI-N):  HI-N was defined as a neutrophil count of < 1 × 10^9^/L at pretreatment and the achievement of an absolute neutrophil increase of ≥ 0.5 × 10^9^/L after treatment;  3) Measurements of white blood cell (WBC), absolute neutrophil and mean changes from baseline.  2. Hematologic improvement-platelet  1) Proportions of patients who achieved absolute increases in platelet counts ≥ 30 × 10^9^/L;  2) Proportions of patients who achieved HI-platelet (HI-P):  HI-P was defined as a platelet increase of ≥ 30 × 10^9^/L among patients with pretreatment levels < 100 × 10^9^/L;  3) Measurements of platelet counts and mean changes from baseline.  **Safety Analyses:**  Safety and tolerability will be assessed by the incidence and severity of AEs and changes from baseline of all relevant parameters, including laboratory test values, physical examination findings, vital signs, and ECOG performance scores. With the exception of haematologic AEs, all AEs will be graded according to the National Cancer Institute Common Toxicity Criteria version 5.0. All subjects will be monitored for AEs within 20 days post-treatment. |
|  |  |

**Abbreviations**

| ADL | Activities of daily living |
| --- | --- |
| AEs | Adverse events |
| Allo-HSCT | Allogeneic hematopoietic stem cell transplantation |
| ANC | Neutrophil |
| AST | Aspartate aminotransferase |
| BM | Bone marrow |
| CRFs | Case report forms |
| ECs | Endothelial cells |
| ECOG | Eastern Cooperative Oncology Group |
| GCP | Good clinical practice |
| Hb | hemoglobin |
| HI-E | Hematologic improvement-erythroid |
| HI-P | Hematologic improvement-platelet |
| HI-N | Hematologic improvement-neutrophil |
| HSCs | Hematopoietic stem cells |
| MDS | Myelodysplastic neoplasm |
| PLT | Platelets |
| RBC-TI | Red blood cell transfusion independence |
| SAEs | Serious adverse events |
| TGF-β1 | Transforming growth factor-beta 1 |
| WBC | White blood cell |

# 1. Introduction

Transforming growth factor-beta 1 (TGF-β1), which is a pleiotropic cytokine, demonstrates context-dependent roles in angiogenesis and tissue repair. Transient TGF-β1 activation promotes vascular stabilization via SMAD2/3-mediated quiescence signals, whereas chronic activation drives fibrosis and inflammation through SMAD1/5 or non-canonical pathways (such as the MAPK pathway).[^2-4^](#_ENREF_1_2) Previous studies have demonstrated that TGF-β1 is highly expressed in bone marrow (BM).[^5^](#_ENREF_1_5) Among the various cells constituting the BM microenvironment, endothelial cells (ECs) exhibit a relatively high expression level of TGF-β1, surpassed only by megakaryocytes and significantly higher than that in osteoblasts, perivascular cells, and reticular cells.[^6^](#_ENREF_1_6) This unique spatial expression pattern provides the foundation for our investigation into the role of TGF-β1 signalling in BM ECs.

Luspatercept (a TGF-β ligand trap) has been reported to improve erythropoiesis in patients with myelodysplastic neoplasm (MDS) and thalassemia,[^7-11^](#_ENREF_1_7) and some clinical trials have suggested potential benefits for white blood cell and platelet counts.[^12-14^](#_ENREF_1_12) However, the ability of luspatercept to promote the recovery of multilineage hematopoiesis by reversing BM EC maladaptation remains unexplored.

This is a prospective single-arm clinical study to evaluate the efficacy and safety of luspatercept for promoting hematopoiesis recovery in patients with poor hematopoietic reconstitution after allo-HSCT.

# 2. Study objectives

## 2.1 Primary Objective

To evaluate the efficacy and safety of luspatercept for promoting hematopoiesis recovery in patients with poor hematopoietic reconstitution after allogeneic hematopoietic stem cell transplantation (allo-HSCT).

## 2.2 Secondary Objectives

To evaluate the influence of luspatercept in the bone marrow microenvironment among patients with poor hematopoietic reconstitution after allo-HSCT.

# 3. Study Design

This is a prospective single-arm clinical study to evaluate luspatercept for promoting hematopoietic recovery in patients with poor hematopoietic reconstitution after allo-HSCT.

Patients with poor hematopoietic reconstitution after HSCT receiving luspatercept treatment will be enrolled, and the dose of luspatercept ranged from 0.7 to 1.4 mg/kg subcutaneously on the basis of routine supportive therapy. The complete blood count will be monitored every 7 days within 20 days from the beginning of luspatercept treatment. The primary endpoint was defined as hematologic improvement-erythroid (HI-E), which included the achievement of red blood cell transfusion independence (RBC-TI) for patients requiring RBC transfusions before administration, as well as a mean Hb increase ≥ 1.5 g/dL for RBC-TI patients at the first administration. The secondary endpoints included proportions of patients who achieved absolute increases in neutrophil ≥ 0.5 × 10^9^/L and platelet counts ≥ 30 × 10^9^/L, respectively; proportions of patients who achieved HI-neutrophil (HI-N) and HI-platelet (HI-P) counts; measurements of white blood cell (WBC), absolute neutrophil and platelet counts; and mean changes from baseline.

All the subjects will be followed for safety and tolerability within 20 days post-treatment. With the exception of haematologic adverse effects (AEs), all AEs will be graded according to the National Cancer Institute Common Toxicity Criteria version 5.0.

AEs= adverse effects; allo-HSCT= allogeneic hematopoietic stem cell transplantation; BM= bone marrow; EC= endothelial cell; HI-E= hematologic improvement-erythroid; HI-N= hematologic improvement-neutrophil; HI-P= hematologic improvement-platelet; MDS= myelodysplastic neoplasm; RBC-TI= red blood cell transfusion independence; TGF-β1= transforming growth factor-beta 1; WBC= white blood cell.

# 4. Subject Selection Criteria

## 4.1 Subject Selection Criteria

### 4.1.1 Number of Subjects

Approximately 64 patients with poor hematopoietic reconstitution after allo-HSCT will receive luspatercept.

### 4.1.2 Inclusion Criteria

Subjects eligible for enrolment in this study must meet all of the following criteria:

1. Poor hematopoietic reconstitution after HSCT receiving luspatercept treatment
2. Aged 18-60 years
3. Comply with the study and follow-up procedures

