# 5. Study Procedures

## 5.1 Screening

Subjects with poor hematopoietic reconstitution after allo-HSCT will be screened for eligibility. Medical history evaluation, vital signs, physical examination, ECOG performance status, blood and urine sampling for laboratory tests, electrocardiogram, chest imaging examination and BM assessment will be performed to determine study eligibility, all of which must be performed ≤3 days prior to enrolment.

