## 5.2 Treatment Allocation and Blinding

This is an open-label study. Neither the subjects nor the investigators will be blinded to the treatment. Upon completion of all the required screening assessments, eligible subjects will receive luspatercept treatment.

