## 5.3 Study Treatment

After enrolment, patients in the study group (luspatercept arm) will be scheduled for luspatercept treatment. If the patients meet the inclusion criteria, they will receive luspatercept (0.7 to 1.4 mg/kg) subcutaneously. In cases of grade 3 or worse AEs (not including haematologic recovery), dose modifications, including dose reductions or interruptions, will be permitted at the discretion of the physician.

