## 5.4 Follow-up

From the beginning of the first administration, the complete blood count will be monitored every 7 days within 20 days.

All the subjects will be followed for safety and tolerability within 20 days after luspatercept treatment. With the exception of haematologic AEs, all AEs will be graded according to the National Cancer Institute Common Toxicity Criteria version 5.0.

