## 6.2 Primary Efficacy Endpoint

1. Hematologic improvement-erythroid (HI-E)

1. For patients requiring RBC transfusions before administration: the achievement of red blood cell transfusion independence (RBC-TI)
2. For RBC-TI patients at the first administration: mean Hb increase ≥ 1.5 g/dL

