# 11. Data Analysis and Statistical Considerations

## 11.1 Study Design Considerations

This is a prospective single-arm clinical study to evaluate luspatercept for promoting hematopoietic recovery in patients with poor hematopoietic reconstitution after allo-HSCT. The dose of luspatercept ranged from 0.7 to 1.4 mg/kg subcutaneously on the basis of routine supportive therapy. In patients with symptoms of drug allergies, such as nausea, vomiting, rash, and bronchospasm, or in patients with disease relapse, the drug will be discontinued immediately.

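### Inclusion criterion 1 makes luspatercept treatment a condition of entry, against Sections 5.2 and 5.3, and nothing in eligibility or in HI-E requires an erythroid deficit for an erythroid primary endpoint

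*Protocol*

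**What the plan says.** **Entry and treatment.** Inclusion criterion 1 (Section 4.1.2, repeated in the Study Synopsis) reads "Poor hematopoietic reconstitution after HSCT receiving luspatercept treatment", and every criterion must be met. Section 3 says the same in a sentence: "Patients with poor hematopoietic reconstitution after HSCT receiving luspatercept treatment will be enrolled". Section 5.2 gives the opposite order: "Upon completion of all the required screening assessments, eligible subjects will receive luspatercept treatment". So does Section 5.3: "After enrolment, patients in the study group (luspatercept arm) will be scheduled for luspatercept treatment".

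**Timing.** Section 5.1 ties the screening tests to enrolment ("all of which must be performed ≤3 days prior to enrolment"), not to the first dose. Section 5.4 starts the blood-count clock at the first dose: "From the beginning of the first administration, the complete blood count will be monitored every 7 days within 20 days".

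**Erythroid deficit.** Poor hematopoietic reconstitution is defined nowhere. There is no haemoglobin, transfusion, neutrophil or platelet limit. Section 6.1 gives HI-N a pretreatment neutrophil limit (below 1 × 10^9/L) and HI-P a pretreatment platelet limit (below 100 × 10^9/L). It only spells out the abbreviation HI-E. Section 6.2 asks transfused patients to reach transfusion independence and all others to show a mean Hb rise of at least 1.5 g/dL, from any starting level. The synopsis bases the analyses on the ITT population.

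**Relapse.** Section 11.1 states that "in patients with disease relapse, the drug will be discontinued immediately". The three exclusions in Section 4.1.3 do not mention relapse.

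**The concern.** There are two separate problems.

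First, a patient who satisfies criterion 1 to the letter is on the drug, and a patient handled under Sections 5.2 and 5.3 is not yet on it. No criterion bars an earlier dose, and the screening window does not refer to the first dose. If a site followed the criterion literally, a patient could be entered after dose 1, once the early course is known. Because the study is open-label, has no control arm and is compared with a fixed 14%, nothing in the design would absorb that selection.

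Second, the primary endpoint is erythroid but the entry rule is not. A patient whose poor reconstitution lies in another lineage is not barred. Such a patient has little room for an Hb rise, and if no response occurs counts as a failure under ITT. The protocol fixed this for neutrophils and platelets but not for the lineage that carries the primary test.

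**Working it through.** **1. The plan's own sample size.** Inputs from Section 11.1.1: reference rate p0 = 0.14, target p1 = 0.28, type I error 5% (sidedness not stated), type II error 20%, expulsion 10%, N = 64. One-sample normal approximation, two-sided 5%:

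n = [1.960·√(0.14·0.86) + 0.842·√(0.28·0.72)]² / (0.28 − 0.14)² = 57.11

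57.11/0.9 = 63.5, so 64. The figure reproduces, and 58 evaluable patients (57.11 rounded up) is a fair working number.

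**2. Dilution.** Let f be the share of enrolled patients with no room for an erythroid response. The protocol gives no value, so f is an assumption, shown over a range. If none of them responds, the overall rate is q = 0.28·(1 − f), and

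power = Φ{[(q − 0.14) − 1.960·√(0.1204/n)] / √(q(1 − q)/n)}

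Example, f = 20%, n = 58: q = 0.224; (0.084 − 0.0893)/0.0547 = −0.097; power 46.1%.

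| f | q | Power, n = 58 | Power, n = 64 |
| --- | --- | --- | --- |
| 0 | 28.0% | 80.5% | 83.6% |
| 10% | 25.2% | 65.5% | 69.1% |
| 20% | 22.4% | 46.1% | 49.2% |
| 30% | 19.6% | 26.1% | 27.9% |

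If 5% of these patients do respond, power at n = 58 is 68.5%, 53.4% and 36.6% for f = 10%, 20% and 30%.

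An exact two-sided test with 58 evaluable (success at 15 or more responders) has 68.9% power undiluted, and 50.4%, 31.0% and 15.0% for the same three shares.

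Keeping all these patients and restoring 80% power (normal approximation, none responding, 10% expulsion) would take 98, 168 or 365 patients. With f = 0, N stays at 64.

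**3. Selection under the literal reading.** Let m be the share of non-responders who start the drug but are never enrolled, again an assumption. A true rate of 14% then appears as 0.14 / [0.14 + 0.86·(1 − m)]. False success at N = 64 is the exact binomial chance of at least 16 responders (two-sided 5% rule) or at least 15 (one-sided 5% rule).

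| m | Apparent rate | ≥16 of 64 | ≥15 of 64 |
| --- | --- | --- | --- |
| 0 | 14.0% | 1.4% | 2.9% |
| 10% | 15.3% | 2.9% | 5.7% |
| 20% | 16.9% | 6.4% | 11.3% |

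**4. Direction.** Dilution lowers the observed rate and costs power, without adding false positives. Selection raises the observed rate. Neither share is known, so the sign of the net effect cannot be given.

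**The case against.** A reader might infer that the trial plans to enrol patients who have already started the drug. The documents do not support that. The criterion does not say so, Sections 4.1.1, 5.2 and 5.3 place treatment after entry, and Section 13.2 puts consent before participation. Loose wording for patients who are to receive luspatercept is the more natural reading. This objection stands. What remains is a contradiction that permits late entry, not a design that intends it.

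A reader might also infer that baseline would be a post-dose value. The endpoint text weighs against this. HI-N and HI-P use pretreatment counts, and the two HI-E groups are set before or at the first administration. A general definition of baseline can also sit in an SAP that is not at hand.

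On dilution, the aim and rationale are multilineage, so a broad entry rule serves the neutrophil and platelet endpoints. Because poor reconstitution is undefined, one cannot say that any particular patient with normal Hb is eligible, only that no rule keeps such a patient out. HI-E also has no Hb ceiling, so some of these patients could respond. These points limit the size of the effect. They do not explain why the primary endpoint alone lacks a pretreatment condition.

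Finally, it is tempting to say that Sections 4.1.3 and 11.1 contradict each other on relapse. They do not. One lists exclusions at entry and the other is a stopping rule. The gap is narrower: Section 5.1 uses a BM assessment to determine eligibility, yet no criterion refers to its result.

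**Conclusion.** The point holds in two parts.

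- **Wording conflict.** Criterion 1, with its repeats in the synopsis and Section 3, cannot be reconciled as written with Sections 5.2 and 5.3. Treatment after enrolment is probably meant. If the literal wording were followed and 10% to 20% of non-responders were lost before entry, false success at 64 patients could reach 2.9–11.3%, against 1.4–2.9% without selection.
- **No erythroid condition.** This part needs no contested reading. If 10% to 30% of entrants cannot respond, power with 58 evaluable falls from 80.5% to between 65.5% and 26.1%, and less steeply if some of them respond.

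All shares are illustrative, since the protocol supplies none. The power figures assume the two-sided normal approximation that reproduces the planned 64. A net bias in either direction is not shown. The amendment is worth making because it is small and a modest dilution is costly.

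**What to change.** 1. Delete the phrase about receiving luspatercept from criterion 1 in Section 4.1.2 and the synopsis, and from the matching sentence in Section 3. State that consent, eligibility and the baseline value all precede the first dose, and that the patient has had no earlier dose in this setting.
2. Define poor hematopoietic reconstitution, and give the primary HI-E analysis a pretreatment erythroid condition: RBC transfusion need, or Hb below a level that the sponsor sets. This can be an entry criterion. Alternatively, it can define the HI-E denominator, with the other patients kept for the neutrophil and platelet endpoints.
3. State how relapse found on the screening BM assessment is handled. No new exclusion is asked for.

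**Cost.** A short amendment and no new test, because the counts and BM assessment are already part of screening. As an entry criterion, the condition would probably slow enrolment slightly, and N = 64 would stand. As a denominator rule, the HI-E analysis would rest on somewhat fewer than the enrolled 64, and the sponsor should check that enough patients remain for the planned power.

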### 4.1.3 Exclusion Criteria

Subjects meeting any of the following criteria will be ineligible for this study:

1. Severe organ injury
2. Uncontrolled active infections
3. Hypersensitivity to luspatercept

## 4.2. Withdrawal Criteria

Subjects will be free to withdraw consent and discontinue participation in the study at any time and without prejudice towards future treatment. A subject's participation in the study may be discontinued at any time at the discretion of the investigator. Justifiable reasons for a subject to be withdrawn from the study include the following:

1. Inability to fully comply with the study protocol

2. Unacceptable toxicity

3. Best interest of the subject based upon the investigator’s discretion

4. At the request of the study subject at any time and for any reason

Subjects will be followed up unless informed consent is withdrawn. The reason for withdrawal from study participation and the date must be documented in the case report form (CRF). The investigator must complete the last visit, including vital signs, physical examination findings, laboratory tests, disease status and AE assessment, all of which must be documented in the CRF.

# 5. Study Procedures

## 5.1 Screening

Subjects with poor hematopoietic reconstitution after allo-HSCT will be screened for eligibility. Medical history evaluation, vital signs, physical examination, ECOG performance status, blood and urine sampling for laboratory tests, electrocardiogram, chest imaging examination and BM assessment will be performed to determine study eligibility, all of which must be performed ≤3 days prior to enrolment.

## 5.2 Treatment Allocation and Blinding

This is an open-label study. Neither the subjects nor the investigators will be blinded to the treatment. Upon completion of all the required screening assessments, eligible subjects will receive luspatercept treatment.

